
|                      |                                                                                                                                                                                                                                                                                                                                                                                                                                                                                                                                                                                                                                                                                                                                                                                                                                                                                                                                                                                                                                                                                                                                                                                                                                                                                                                                                                                                                                                                                                                                                                                                                                                                                                                                                                                                                                                                                                                                                                                                                                                                                                                                                                                                                                                                                                                                                                                                                                                                                                                                                                                                                                                                                                                                                                                                                                                                                                                                                                                                                                                                                                                                                                                                                                                                                                                                                                                                                                                                                                                                                                                                                                                                                                                                                                                                    |
|----------------------|----------------------------------------------------------------------------------------------------------------------------------------------------------------------------------------------------------------------------------------------------------------------------------------------------------------------------------------------------------------------------------------------------------------------------------------------------------------------------------------------------------------------------------------------------------------------------------------------------------------------------------------------------------------------------------------------------------------------------------------------------------------------------------------------------------------------------------------------------------------------------------------------------------------------------------------------------------------------------------------------------------------------------------------------------------------------------------------------------------------------------------------------------------------------------------------------------------------------------------------------------------------------------------------------------------------------------------------------------------------------------------------------------------------------------------------------------------------------------------------------------------------------------------------------------------------------------------------------------------------------------------------------------------------------------------------------------------------------------------------------------------------------------------------------------------------------------------------------------------------------------------------------------------------------------------------------------------------------------------------------------------------------------------------------------------------------------------------------------------------------------------------------------------------------------------------------------------------------------------------------------------------------------------------------------------------------------------------------------------------------------------------------------------------------------------------------------------------------------------------------------------------------------------------------------------------------------------------------------------------------------------------------------------------------------------------------------------------------------------------------------------------------------------------------------------------------------------------------------------------------------------------------------------------------------------------------------------------------------------------------------------------------------------------------------------------------------------------------------------------------------------------------------------------------------------------------------------------------------------------------------------------------------------------------------------------------------------------------------------------------------------------------------------------------------------------------------------------------------------------------------------------------------------------------------------------------------------------------------------------------------------------------------------------------------------------------------------------------------------------------------------------------------------------------------|
|                      | 
subjects in a dose group have a dose limiting toxicity defined as a Grade 3 or more than one subject in a dose group have a dose-limiting toxicity defined as a Grade 4 AE related to the investigational drug, the dose escalation may be stopped through discussion.
                                                                                                                                                                                                                                                                                                                                                                                                                                                                                                                                                                                                                                                                                                                                                                                                                                                                                                                                                                                                                                                                                                                                                                                                                                                                                                                                                                                                                                                                                                                                                                                                                                                                                                                                                                                                                                                                                                                                                                                                                                                                                                                                                                                                                                                                                                                                                                                                                                                                                                                                                                                                                                                                                                                                                                                                                                                                                                                                                                                                                                                                                                                                                                                                                                                                                                                                                                                                                                                                                                                      |
| Study Evaluations    | 
 
• Safety and Tolerability Evaluation 
 
➢ Adverse events (AEs) including subjective/objective symptoms and signs etc.,
 
➢ Vital signs, physical examinations, clinical laboratory tests, 12-lead ECGs
 
➢ Neurologic examination (Full or brief)
 
 
 
• Pharmacokinetic Evaluation 
Single ascending dose study(30 mg, 60 mg, 240 mg, 480 mg, 960 mg)
 
 
➢ Blood sampling timepoints: 1d 0h (pre-dose), 0.33, 0.75, 1, 2, 3, 4, 6, 8, 12, 24, 48, 72, 96, 120, 144 h post-dose
 
➢ Urine collection intervals: 1d 0h (pre-dose baseline spot-urine), 0 ~ 12h, 12 ~ 24h (2d 0h), 24 ~ 48h (3d 0h), 48 ~ 72h (4d 0h) post-dose
 
➢ Primary endpoints: <math>AUC_{last}</math>, <math>AUC_{inf}</math>, <math>C_{max}</math>, <math>T_{max}</math>, <math>t_{1/2}</math>, <math>CL/F</math>, <math>V_z/F</math>, <math>fe</math>, <math>CL_R</math> for KDS2010
 
➢ Secondary endpoints: <math>AUC_{last}</math>, <math>AUC_{inf}</math>, <math>C_{max}</math>, <math>T_{max}</math>, <math>t_{1/2}</math>, metabolic ratio for KDS8170(main metabolite of KDS2010)
 
 
Single dose study(120 mg, Food effect study)
 
 
➢ Blood sampling timepoints: 1d 0h (pre-dose), 0.33, 0.75, 1, 2, 3, 4, 6, 8, 12, 24, 48, 72, 96, 120, 144 h post-dose in phase 1 and 2
 
➢ Urine collection intervals: 1d 0h (pre-dose baseline spot-urine), 0 ~ 12h, 12 ~ 24h (2d0h), 24 ~ 48h (3d0h), 48 ~ 72h (4d0h) post-dose in phase 1 and 2
 
➢ Primary endpoints: <math>AUC_{last}</math>, <math>AUC_{inf}</math>, <math>C_{max}</math>, <math>T_{max}</math>, <math>t_{1/2}</math>, <math>CL/F</math>, <math>V_z/F</math>, <math>fe</math>, <math>CL_R</math> for KDS2010
 
➢ Secondary endpoints: <math>AUC_{last}</math>, <math>AUC_{inf}</math>, <math>C_{max}</math>, <math>T_{max}</math>, <math>t_{1/2}</math>, metabolic ratio for KDS8170(main metabolite of KDS2010)
 
 
Multiple ascending dose study(60mg, 120 mg, 240 mg, 480 mg, 120 mg(elderly))
 
 
➢ Blood sampling timepoints: 1d 0h (pre-dose), 0.33, 0.75, 1, 2, 3, 4, 6, 8, 12h, 2d 0h(pre-dose), 3d 0h(pre-dose), 4d 0h(pre-dose), 5d 0h(pre-dose), 6d 0h(pre-dose), 7d 0h(pre-dose), 0.33, 0.75, 1, 2, 3, 4, 6, 8, 12, 24 h (8d 0h), 9d 0h, 10d 0h, 11d 0h, 12d 0h, 13d 0h post-dose
 
➢ Urine collection intervals: 1d 0h (pre-dose baseline spot-urine), 0 ~ 12h, 12 ~ 24h (2d 0h), 7d 0h (pre-dose baseline spot-urine), 0 ~ 12h, 12 ~ 24h (8d 0h), 24 ~ 48h (9d 0h), 48 ~ 72h (10d 0h) post-dose
 
➢ Primary endpoints: <math>AUC_{tau}</math>, <math>C_{max,ss}</math>, <math>C_{min,ss}</math>, <math>C_{av,ss}</math>, <math>T_{max,ss}</math>, <math>t_{1/2}</math>, PTF (peak to trough fluctuation ratio), <math>CL_{ss}/F</math>, <math>V_{d,ss}/F</math>, <math>fe</math>, <math>CL_R</math>, accumulation ratio (Ra) for KDS2010
 
➢ Secondary endpoints: <math>AUC_{tau}</math>, <math>C_{max,ss}</math>, <math>C_{min,ss}</math>, <math>C_{av,ss}</math>, <math>T_{max,ss}</math>, <math>t_{1/2}</math>, PTF (peak to trough fluctuation ratio), accumulation ratio (Ra), metabolic ratio for KDS8170(main metabolite of KDS2010)
 
 
• Exploratory Pharmacodynamic Evaluation 
Multiple ascending dose study (60mg, 120 mg, 240 mg, 480mg, 120 mg(elderly))
 
 
➢ Blood sampling timepoints: 1d/7d 0h (pre-dose), 2, 24h post-dose
 
➢ Endpoints: MAO-B activity
 
 
 

 |
| Statistical Analysis | 
 
• Safety and Tolerability Analysis 
For safety/tolerability analysis, the abnormal findings observed in safety evaluation lists such as the occurrence pattern of adverse events, vital signs and clinical laboratory results are described, and if necessary, each list is compared according to appropriate classification such as dosing group. Medical history and AEs are coded using the MedDRA (ver. 24.0 or later).
 
 
• Pharmacokinetic Analysis 
After calculating pharmacokinetic parameters for each subject by noncompartmental methods using an appropriate and validated pharmacokinetic software (Phoenix WinNonlin® version 8.0 or newer,
 
 
                                                                                                                                                                                                                                                                                                                                                                                                                                                                                                                                                                                                                                                                                                                                                                                                                                                                                                                                                                                                                                                                                                                                                                                                                                                                                                                                                                                                                                                                                                                                                                                                                                                                                                                                                                                                                                                                                                                                                                                                                                                                                                                                                                                                                                                                                                                                                                                                                                                                                                                                                                                                                                                                                                                                                                                                                                                                                                                                                                                                                                                     |

|  |                                                                                                                                                                                                                                                                                                                                                                                                                                                                                                                                                                                                                                                                                                                                                                                                                                                                                                                                                                                                                                                                                                                                                                                                                                |
|--|--------------------------------------------------------------------------------------------------------------------------------------------------------------------------------------------------------------------------------------------------------------------------------------------------------------------------------------------------------------------------------------------------------------------------------------------------------------------------------------------------------------------------------------------------------------------------------------------------------------------------------------------------------------------------------------------------------------------------------------------------------------------------------------------------------------------------------------------------------------------------------------------------------------------------------------------------------------------------------------------------------------------------------------------------------------------------------------------------------------------------------------------------------------------------------------------------------------------------------|
|  | 
Certara, CA, USA), descriptive statistics are summarized by appropriate classification such as dosing group.
 
To evaluate the pharmacokinetic linearity according to the dose increase, the relationship between <math>C_{\max}</math>, AUC(<math>AUC_{\text{inf}}</math>, <math>AUC_{\text{last}}</math>) and the administered dose is evaluated through regression analysis, and <math>C_{\max}</math>, AUC corrected for the administered dose are compared between dosing groups through a parametric or non-parametric statistical test. In addition, parameters such as <math>T_{\max}</math>, <math>t_{1/2}</math>, CL/F can be compared between dosing groups through an appropriate method.
 
Food effect evaluation is performed by calculating the geometric mean ratio (GMR) of the pharmacokinetic parameters (<math>C_{\max}</math>, AUC) after a high-fat meal to the fasting and its 90% confidence interval (CI).
 

• Exploratory Pharmacodynamic Analysis

 
After calculating exploratory pharmacodynamic parameters for each subject, descriptive statistics are summarized by appropriate classification such as dosing group.
 |
|--|--------------------------------------------------------------------------------------------------------------------------------------------------------------------------------------------------------------------------------------------------------------------------------------------------------------------------------------------------------------------------------------------------------------------------------------------------------------------------------------------------------------------------------------------------------------------------------------------------------------------------------------------------------------------------------------------------------------------------------------------------------------------------------------------------------------------------------------------------------------------------------------------------------------------------------------------------------------------------------------------------------------------------------------------------------------------------------------------------------------------------------------------------------------------------------------------------------------------------------|

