|   |        | Test group    | KDS2010 240 mg × 4         | 6 |
|   |        | Control group | KDS2010 240 mg placebo × 4 | 2 |

†For cohort 3, a fixed sequence, 2 period, cross over study will be conducted to evaluate the effect of food on the bioavailability of KDS2010. (If the dose escalation plan is changed, the dose for the evaluation of food effects may also be changed.)

• Multiple ascending dose study††: Total 40 subjects

| Cohort | Dosing groups    | Dosage        |                            | Number of subjects |
|--------|------------------|---------------|----------------------------|--------------------|
| 1      | 60 mg            | Test group    | KDS2010 30 mg × 2          | 6                  |
|        |                  | Control group | KDS2010 30 mg placebo × 2  | 2                  |
| 2      | 120 mg           | Test group    | KDS2010 30 mg × 4          | 6                  |
|        |                  | Control group | KDS2010 30 mg placebo × 4  | 2                  |
| 3      | 240 mg           | Test group    | KDS2010 240 mg × 1         | 6                  |
|        |                  | Control group | KDS2010 240 mg placebo × 1 | 2                  |
| 4      | 480 mg           | Test group    | KDS2010 240 mg × 2         | 6                  |
|        |                  | Control group | KDS2010 240 mg placebo × 2 | 2                  |
| 5      | 120 mg (elderly) | Test group    | KDS2010 30 mg × 4          | 6                  |
|        |                  | Control group | KDS2010 30 mg placebo × 4  | 2                  |

††In the case of a multiple ascending dose study, subjects are administered once a day for 7 days.

Subjects

• Inclusion Criteria

1) Young subjects: Healthy Korean or Caucasian volunteers between 19 and 45 years of age at the screening visit  
Elderly subjects: Healthy Korean volunteers over 65 years and under 85 years of age at the screening visit  
※ Caucasian who were born in Europe, have lived outside Europe for less than 10 years, and both parents and grandparents were of European origin

2) Women: Except for surgical infertility (bilateral fallopian tube occlusion, hysterectomy, bilateral salpingectomy, bilateral oophorectomy, etc.), those who tested negative in the urine pregnancy test (hCG) performed at screening

3) Subjects with body weight between 55.0 kg and 90.0 kg and Body Mass Index (BMI) between 18.0 kg/m² and 30.0 kg/m² at the screening visit  

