※ Body Mass Index = body weight(kg)/ [height(m)]²

4) Subjects who completely understand the nature of study and make a voluntary decision to participate in this clinical study and provide the informed consent.

5) Subjects who are considered to be suitable to participate in this study based on physical examination, clinical laboratory test results and medical history

• Exclusion Criteria

1) Subjects with a clinical evidence or history of hepatic, renal, neurologic, immunologic, respiratory, endocrine, hematologic, oncologic, cardiovascular, psychiatric disease (However, in the case of an elderly person with a history of mild disease, participation is possible if the researcher determines that the drug can be discontinued at least 2 weeks before the expected first dose or 5 times or more before the half-life.)

2) Subjects with a history of gastrointestinal disease (e.g., gastrointestinal ulcers, gastritis, stomach cramp, gastroesophageal reflux disease, Crohn’s disease, etc.) or surgery (except for simple appendectomy or herniotomy), which can influence the safety and pharmacokinetic evaluation of investigational drugs

3) For all women of childbearing age, except for surgical infertility, those who are pregnant, may be pregnant, or are lactating

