## 9.2. Inclusion Criteria/Exclusion Criteria

### 9.2.1. Inclusion Criteria

- 1) Young subjects: Healthy Korean or Caucasian volunteers between 19 and 45 years of age at the screening visit

Elderly subjects: Healthy Korean volunteers over 65 years and under 85 years of age at the screening visit

※ Caucasian who were born in Europe, have lived outside Europe for less than 10 years, and both parents and grandparents were of European origin.

- 2) Women: Except for surgical infertility (bilateral fallopian tube occlusion, hysterectomy, bilateral salpingectomy, bilateral oophorectomy, etc.), those who tested negative in the urine pregnancy test (hCG) performed at screening
- 3) Subjects with body weight between 55.0 kg and 90.0 kg and Body Mass Index (BMI) between 18.0 kg/m^2 and 30.0 kg/m^2 at the screening visit

※ Body Mass Index = body weight(kg)/ [height(m)]

- 4) Subjects who completely understand the nature of study and make a voluntary decision to participate in this clinical study and provide the informed consent.

- 5) Subjects who are considered to be suitable to participate in this study based on physical examination, clinical laboratory test results and medical history

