- 10) Subjects who had taken or are expected to take any prescription drug or herbal medicine within 2 weeks or any over the counter (OTC) drug within 1 week prior to the first administration day (however, subjects fulfilling other conditions could participate in the study at the investigator's discretion)

- 11) Subjects who had taken an inducer or inhibitor of drug metabolism such as barbiturates etc. within 1 month prior to the first administration day
- 12) Subjects who had participated in another clinical study (including bioequivalence studies) within 6 months prior to the first administration day
- 13) Subjects who had donated whole blood or component blood, or received transfusion within 3 months prior to the first administration day
- 14) Subjects who drink continuously (more than 21 units/week, 1 unit = 10 g of pure alcohol) or are unable to stop drinking during the period from 3 days prior to the first administration day to the end of the study
- 15) Smokers(except for whom quitted smoking prior to the first administration day for at least 3months) or who cannot stop smoking during the period from 3 months prior to the first administration day to the end of the study
- 16) Subjects who cannot stop taking grapefruit or food containing grapefruit during the period from 3 days prior to the first administration day to the end of the study
- 17) Subjects who have taken excessive amounts of caffeine (> 5 units/day) on a continuous basis or who cannot stop taking caffeine or food containing caffeine (coffee, tea(black tea, green tea, etc.), carbonated drink, coffee-flavored milk, nutritional tonics, etc.) during the period from 3 days prior to the first administration day to the end of the study
- 18) During the entire study period and for at least 3months after the last administration of the investigational drug, subjects who are unable to use an appropriate, medically accepted double contraception method or medically acceptable contraceptive method for themselves or their spouse or partner and who do not agree not to donate sperm by that period.
  - ※ Medically acceptable contraceptive methods
    - ✓ Use of an intrauterine device with a proven rate of pregnancy failure in the spouse (or partner)
    - ✓ Simultaneous use of a barrier contraception (for male or female) and spermicide
    - ✓ Surgery of the person himself or his spouse(or partner) (vasectomy, salpingectomy/ligation, hysterectomy)

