- 19) Otherwise, subjects judged by the investigator to be inappropriate for inclusion in the study

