#### **9.4. Replacement of Study Subjects**

In this clinical study, a small number of candidate subjects can be registered in advance in consideration of the dropout rate prior to the first administration, and when dropout occurs before the first administration, the candidate subject can be replaced with the formal subject.

As this clinical study is conducted for exploratory purposes, not hypothesis testing, there is no need to replace subjects even if they drop out. In order to maintain the ratio of subjects receiving the test drug to subjects receiving placebo by dose group, additional subjects may be registered to replace subjects who dropped out. However, in the case of a subject who dropped out due to an adverse event that occurred after administration of the investigational drug, the subject is not replaced.

In the case of replacing a subject who dropped out due to reasons other than adverse events (eg, withdrawal of consent, etc.), replaced subjects are selected in the order that they passed the screening test, and the subject number that has already been used cannot be used. In the case of subject replacement, the subject number of the subject to be replaced shall be marked so that it can be recognized that it is the replaced subject, including the last digit of the number of the subject who dropped out.

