## 4) Pregnancy test

For all women of childbearing potential except surgical infertility, urine hCG test is performed before - 1d randomization.

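### As worded, exclusion 3 extends the surgical-infertility exemption to lactation, so no explicit criterion bars a breastfeeding, surgically sterile woman aged 19 to 45.

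*Protocol*

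**What the plan says.** Exclusion 3 appears in the same words in the synopsis and in 9.2.2: "For all women of childbearing age, except for surgical infertility, those who are pregnant, may be pregnant, or are lactating".

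Inclusion 2, in the synopsis and in 9.2.1, says what counts as surgical infertility and exempts those women from the screening pregnancy test: "Except for surgical infertility (bilateral fallopian tube occlusion, hysterectomy, bilateral salpingectomy, bilateral oophorectomy, etc.), those who tested negative".

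Women are eligible in the young cohorts. Inclusion 1 sets an age range and does not limit entry to men: "Young subjects: Healthy Korean or Caucasian volunteers between 19 and 45 years of age at the screening visit".

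Two further criteria rest on judgement and do not mention lactation. Inclusion 5 requires "Subjects who are considered to be suitable to participate in this study based on physical examination, clinical laboratory test results and medical history". Exclusion 19 is the general clause: "Otherwise, subjects judged by the investigator to be inappropriate for inclusion in the study".

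**The concern.** Surgical sterility is a sound reason to waive a pregnancy condition, because it removes the possibility that the condition addresses. It gives no reason to waive a lactation condition: a woman whose tubes have been occluded or removed can still be breastfeeding. Exclusion 3 puts both kinds of condition under one exemption, and the exemption fits only the first kind.

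The sponsor wrote lactation into the criterion, so the evident intent is to keep lactating women out. For one definable group the literal text does not do that, and the decision passes to the investigator's judgement. What is at stake is the safety of a possible third party, the nursing infant, in a phase 1 study whose nonclinical summary (5.1.3) reports nothing on transfer into milk. The analysis is not at stake.

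**Working it through.** No arithmetic applies. The check reads the criterion for scope and then looks for any other rule that would catch the woman it lets through.

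**Scope of the exemption.** The sentence first sets the population (women of childbearing age, less the surgically infertile) and then lists the conditions (pregnant, possibly pregnant, lactating). An exception placed in the population clause applies to every condition after it. The synopsis and 9.2.2 carry the same words, so neither corrects the other.

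**Test case.** Take a healthy woman aged 19 to 45 with bilateral tubal occlusion who is breastfeeding, and who meets the ethnicity, weight, vital-sign, laboratory and ECG limits.

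| Rule | Result for this woman |
|---|---|
| Inclusion 1 (age, ethnicity) | Met |
| Inclusion 2 (negative hCG test) | Exempt, because tubal occlusion is listed |
| Exclusion 3 (pregnant, possibly pregnant, lactating) | Not triggered; she is outside its population |
| Exclusion 18 (contraception) | Not triggered on contraceptive method; the acceptable methods include "Surgery of the person himself or his spouse(or partner) (vasectomy, salpingectomy/ligation, hysterectomy" |
| Pregnancy tests in 10.7.1 and 10.7.2 | Not done: "For all women of childbearing potential except surgical infertility, urine hCG test is performed" |
| Other specific criteria in 9.2 | None concerns lactation |
| Prohibited items and restrictions in 10.4.4 and 10.8 | Silent on breastfeeding |
| Inclusion 5 and exclusion 19 | Could keep her out, by judgement |

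Two premises are used. First, tubal occlusion is treated as equivalent to the ligation named in exclusion 18. Second, tubal occlusion and salpingectomy do not stop lactation; this is ordinary physiology and is not stated in the protocol.

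**Remaining safeguards.** Screening (10.7.1) includes a physical examination and a medical history reaching back 3 years, so a recent delivery and sterilisation would ordinarily come to light. Section 17.4 requires the investigator to check each subject's health before enrolment. These steps inform the judgement under inclusion 5 and exclusion 19, but none of them names lactation.

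**Result.** Every explicit criterion is satisfied. Exclusion 3 is the only mention of lactation in the protocol text available for review.

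**The case against.** The strongest case on the other side is that the intent is plain and the text is simply awkward. The phrase about surgical infertility recurs wherever hCG testing is described, and there it concerns pregnancy only; exclusion 3 most plausibly carries it over. A sensible investigator would read it that way and would decline a breastfeeding volunteer under inclusion 5 or exclusion 19. The setting also makes the case remote, because subjects stay in the unit from the day before dosing until day 4 (single dose) or day 10 (multiple dose). The consent form is only listed as Annex 1, and the screening step on subject precautions is not spelled out, so an instruction on breastfeeding may exist there.

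Most of this stands. It makes the event unlikely and marks the defect as one of drafting. It does not remove the defect, because a written exclusion should not depend on the investigator setting aside its literal wording.

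Several stronger readings are tempting, and the documents do not support them.

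- A reader might infer that exclusion 19 is the only remaining barrier. Inclusion 5 is a second one, and the screening history and examination feed both.
- A reader might size the problem by counting everyone in the young cohorts. That count includes men and all women who are not both sterilised and breastfeeding, so it does not measure the affected group.
- A reader might use the expected half-life in 5.2.2 to calculate drug remaining in the mother at discharge. Such a figure says nothing about transfer into milk or exposure of an infant.
- A reader might infer that monitoring would miss such an enrolment. Section 17.5 has monitors review recruitment and compare records with source data, so this cannot be asserted.
- A reader might infer that the sponsor chose to admit lactating women. Naming lactation as an exclusion points the other way.

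**Conclusion.** The point holds as a wording defect. Followed literally, exclusion 3 leaves a lactating, surgically sterile woman aged 19 to 45 barred by no explicit criterion, and her exclusion rests on investigator judgement alone.

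Its size is small. The affected group is the overlap of several uncommon conditions, and the protocol gives no figure for any of them, so no number is offered. No endpoint, sample size, analysis or escalation rule is touched; the study describes itself in 9.4 in these terms: "As this clinical study is conducted for exploratory purposes, not hypothesis testing".

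The conclusion rests on the grammatical scope of the exemption, on the list of procedures in inclusion 2, and on the absence of any other lactation rule in the protocol text available. An instruction in the consent form or in the subject-precaution material would lessen the practical risk but would not correct the criterion.

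**What to change.** Reword exclusion 3 in the synopsis and in 9.2.2, identically, so that it has two separate limbs:

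1. Women who are lactating are excluded, without the surgical-infertility exemption.
2. Women who are pregnant or may be pregnant are excluded, and the surgical-infertility exemption attaches to this limb only.

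Inclusion 2 and the pregnancy-test sections can stay as they are, since the exemption there concerns pregnancy alone.

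The cost is one line of text in two places at the next amendment. It adds no test, visit or subject. The only downside is that at most a very few volunteers become ineligible.
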